***The Implementation Process: Organizational Level***

The implementation plan embraces four fundamental principles:

1) Developing local program expertise is important for sustaining model competency and fidelity. Involvement of model developers and practice experts should be front-loaded, then roles shift to local experts as they are developed.

2) Direct coaching and modeling in the actual practice setting is critical for optimal provider skill acquisition.

3) Maintaining and monitoring fidelity across time is critical. Adaptations to the local context or evolutionary changes in the model should be carefully planned, transparent and systematically implemented rather than made idiosyncratically or haphazardly.

4) Policy leadership and funding structures are important for institutionalizing the new practice model.

Phase One: Evaluation of Organizational Characteristics and Training of Staff and Delivery of Comparison Condition Intervention. Two trained ethnographers from the Ciudad Juárez training center will administer computer-based questionnaires to **ten staff (the director, intervention counselors, and supervisors).** The ethnographers will then conduct individual, semi-structured qualitative interviews with each participating staff member, and finally they will carry out a focus group session with all the participants at once in order to assess relevant provider and organizational factors. The questionnaires, the individual interviews, and the focus group session will all last about an hour each, and they will be tape-recorded. Provider factors to be assessed include: attitudes toward adoption of innovation (e.g., intuitive appeal of intervention program); personal disposition (e.g., adaptability, change catalyst); knowledge and perceived utility of intervention; and socio-demographic characteristics. Organizational factors include: leadership qualities; organization culture and climate (e.g., work attitudes, autonomy); organizational support (e.g., support for creativity); and social influence (e.g., teamwork). The same battery of assessments was used by [name] in a study of a children’s service agency (see [name], item 5 in Bibliography). A copy of that assessment battery is provided in Appendix 2. The measures have all been translated into Spanish, and the name of the organization has been changed to fit the new study.

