***Data Analysis and Interpretation***

Aim 1: Equivalence testing will be used to evaluate Aim 1 using Schuirmann’s (1987) test of equivalence. A nominal alpha of .05 will be used in the proposed analysis. Given the nested data structure (i.e., service providers nested in CBOs), hierarchical linear modeling will be used to adjust standard errors for possible dependency among observations. The outcome of interest in Aim 1 focuses on *Mujer Segura* fidelity. We expect that service providers will attain approximately 90% treatment fidelity when considering that 100% is perfect fidelity.

Power calculations for equivalence tests proposed for Aim 1 were conducted using SAS® Proc Power. Using the bounds and nominal alpha specified above, along with a hypothesized difference between population group means of zero and a standard deviation of 15 in each group, the proposed sample size of 120 (10 staff x 12 CBOs) would yield power of >.89 to reject the null hypothesis of mean differences in favor of the alternative of group equivalence. This power calculation is based on the assumption that observations are independent. If the observations are dependent, this will be an overestimate of statistical power. One method of calculating power in this case is to estimate the degree to which the variance will be increased due to non-independence. Specifically, the variance will be increased by a factor of 1+(m-1)*ICC, also known as the design effect, where m is the average cluster size and ICC is the intraclass correlation coefficient. While we don’t have prior ICCs for *Mujer Segura* fidelity ratings, in our work examining service provider attitudes toward EBI implementation in CBOs, ICCs were generally low. However, in a larger and more representative study of CBOs across the U.S., the ICC was .03, and we expect the fidelity ICC to be of similar magnitude. Using the average ICC of .03 from this recent study, and an average cluster size of 8, the variance is estimated to be increased by a factor of 1.21. Given a total sample size of 96, the functional sample size would be 79.34 (i.e., total sample size/design effect), which would yield power of .80.

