Aim 2: Analyses will be informed by the conceptual model proposed by [name] and adapted for this study in which implementation of EBI results in effects of organizational and provider characteristics on provider attitudes, fidelity and outcomes. Conversely, introduction of an EBI can impact organizational and—to a lesser extent—provider characteristics. In particular, we will examine changes in organizational processes (i.e., culture, climate) and group process characteristics (e.g., organizational support) as a function of *Mujer Segura* implementation. We will also examine the relationship between individual organizational factors and provider characteristics, and their impact on the implementation of *Mujer Segura*. We will then examine whether more knowledge and higher levels of perceived utility are associated with better fidelity and outcomes. In all CBOs, we will examine the degree to which Leadership and Organizational Support are associated with more positive Attitudes Toward Evidence-Based Practice, fidelity, and outcomes. We will also examine the degree to which Personal Dispositional Innovativeness and other provider characteristics such as age, education level, experience, and job tenure are associated with Attitudes Toward Evidence-Based Interventions, fidelity, and outcomes. Quantitative hypotheses to be examined include:

2a) More positive organizational culture and climate will be associated with more positive attitudes toward EBI.

2b) Personal dispositional innovativeness will mediate the relationship between staff demographics and attitudes toward EBI. Specifically, staff demographics (i.e., higher education level, shorter job tenure) will be associated with higher personal dispositional innovativeness, and personal dispositional innovativeness will be positively associated with attitudes toward EBI.

2c) Social networks indicating more connectivity and positive information regarding *Mujer Segura* will be positively associated with attitudes toward EBI.

2d) Attitudes toward EBI will meditate the relationship between personal dispositional innovativeness and implementation fidelity. Specifically, personal dispositional innovativeness will be positively associated with attitudes toward EBI, and attitudes toward EBI will be positively associated with implementation fidelity.

2e) More positive attitudes toward EBI will be associated with greater implementation fidelity.

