2f) Greater fidelity will be associated with more positive FSW outcomes.

In order to examine components of relationships described in 2a-2f, analyses will use HLM in order to adjust standard errors for possible dependency among observations. Significance tests will use an alpha of .05 (two-tailed). Analyses will consist of correlations (2c, 2e, 2f), regression (2a), and tests of mediation (2b, 2d). Mediation or indirect effects will be tested using confidence intervals. Given that bootstrapping confidence intervals will likely not be an option in this study due to missing data (although missing data will be handled through multiple imputation methods [described above] for bootstrapping from a series of imputed data sets are not available), intervals will be constructed based on the distribution of the product of two random variables. This method of significance testing is superior to non-resampling alternatives in terms of having greater Type I error rate accuracy and higher power. The intervals will be estimated using PRODCLIN.

Power was calculated under the assumptions of independent and dependent observations for the proposed correlation, regression, and mediation tests. Under independence the sample size used was the total of 96 and under dependence (ICC = .03) a functional sample size of 79.34 was used (see Aim1). Power for the correlation hypotheses was evaluated using SAS® Proc Power. The power to detect a medium effect size (r = .30) for correlation hypotheses was calculated to be .85 under independence and .78 under dependence. Power for the regression hypotheses was evaluated using the Monte Carlo facility of Mplus with 20,000 replications. All parameters of the regression model were set to be medium effect sizes based on bivariate association conventions, that is, the correlation between each predictor and the outcome and the correlation among the predictors was set to be *r* = .30. The power for each regression coefficient was calculated to be .79 under independence and .71 under dependence. Finally, for tests of mediation, simulations by Fritz and Mackinnon suggest that the sample size needed for power of .80 using the proposed distribution of the product of two random variables approach (i.e., PRODCLIN) is 74, when the effect sizes for both paths are medium (i.e., ==.39). The total N of 96 used under the assumption of independence and 79.34 under dependence will be sufficient to achieve power of .80.

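### Hypothesis 2a is about the culture and climate of 12 organizations, but it is powered only as a regression on 96 staff, with the level of the predictors left open; .79/.71 should not be read as power for an organization-level effect

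*Protocol*

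**What the plan says.** All references are to the protocol, section 8.

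- **Hypothesis.** Data Analysis and Interpretation, Aim 2, states 2a as "More positive organizational culture and climate will be associated with more positive attitudes toward EBI".
- **Type of construct.** The Implementation Process: Organizational Level (Phase One) lists provider factors and organizational factors separately: "Organizational factors include: leadership qualities; organization culture and climate". The data come from questionnaires that about ten staff per CBO complete individually. No aggregation to CBO level is described.
- **Analysis.** 2a is a regression, and "analyses will use HLM in order to adjust standard errors for possible dependency among observations". Tests are two-sided at .05.
- **Power.** "Under independence the sample size used was the total of 96"; under dependence a functional 79.34 was used. All predictor-outcome and predictor-predictor correlations were set to .30. Result: "The power for each regression coefficient was calculated to be .79 under independence and .71 under dependence".
- **ICC.** Under Aim 1, "in a larger and more representative study of CBOs across the U.S., the ICC was .03". There it serves to anticipate the ICC of fidelity, and the outcome it was measured on is not named. Aim 2 then applies .03 to its own tests.

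No power figure for Aim 2 rests on 12 CBOs.

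**The concern.** An organization's culture is a property of the organization, and there are 12 organizations. A sample of 96 people informs 2a in two different ways:

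- It can compare CBOs with one another, which is what the hypothesis asks.
- It can compare colleagues in one CBO who see the same workplace differently. That is a question about perception.

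An HLM used only to correct standard errors blends the two into one slope. The power calculation does not distinguish them either.

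Two things are at stake. A significant pooled slope could be reported as an effect of organizational culture when most of its information is within-CBO. And a reader could take .79/.71 as the chance of detecting an organization-level relation, when that chance may be much lower.

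**Working it through.** **Inputs from the protocol.** K = 12 CBOs; m = 8 staff per CBO in the power calculation (10 planned, 120 in all); ICC = .03; r = .30; two-sided α = .05.

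**1. The plan's own figures.** Design effect 1 + 7 × .03 = 1.21, and 96/1.21 = 79.34, as stated. The figures .79/.71 are matched (.792/.711) with two predictors correlated .30, raw coefficients of .30 and residual variance 1. With predictor-outcome correlations of .30, as the text says, two predictors give .63/.55. That is a separate matter; the point here is the level of the predictors.

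**2. If individual ratings are entered.** r = .30 is attainable. The question is where the pooled slope gets its information. Let ρ be the ICC of the culture scores (not given in the protocol; an assumption) and .03 the residual ICC of attitudes.

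- Within-CBO information: K(m−1)(1−ρ)/.97.
- Between-CBO information: (K−1)(mρ + 1 − ρ)/(.97 + 8 × .03) = 11(mρ + 1 − ρ)/1.21.
- ρ = .05: 82.3 and 12.3, so 87% within.
- ρ = .50: 43.3 and 40.9, so 51% within.

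**3. If CBO values are entered.** Assume that .03 is the unconditional ICC of attitudes. A predictor constant within a CBO can explain at most the between-CBO share of an individual's score, so |r| ≤ √.03 = .173. Conversely, r = .30 needs an ICC of at least .30² = .09. The factor 1 + (m−1)ICC is itself the inflation for a predictor constant within clusters, so on this reading .71 pairs a CBO-level inflation with an effect size above the cap.

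**4. Power on 12 CBO means.** Let f be the fraction of between-CBO variance that culture explains. The residual variance of a CBO mean is v = ICC(1−f) + (1−ICC)/m, and the noncentrality is √(12 × f × ICC / v), with a t test on 10 df.

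- m = 8, f = 1: v = .97/8 = .12125; √(.36/.12125) = 1.72; power .34.
- m = 8, f = .5: v = .015 + .12125 = .13625; √(.18/.13625) = 1.15; power .18.
- m = 10, f = 1: v = .097; noncentrality 1.93; power .41.
- m = 10, f = .5: v = .112; noncentrality 1.27; power .21.

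**5. Best case (f = 1) by other methods.**

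| Method | 96 staff | 120 staff |
|---|---|---|
| 12 CBO means, Fisher z (rough at 12 points) | .30 | .36 |
| 12 CBO means, simulated | .31 | .38 |
| 12 CBO means, noncentral t | .34 | .41 |
| All staff, ordinary regression, simulated | .36 | .44 |
| All staff, noncentral t at r = .173 | .40 | .48 |

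The individual-level rows are legitimate here: when the predictor explains all between-CBO variance, no residual clustering is left.

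**6. Sensitivity to the ICC** (m = 8, 10 df): best-case power is .15 at ICC .01, .53 at .05 and .84 at .10. If culture explains half the between-CBO variance, the figures are .10, .26 and .41.

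**The case against.** Four points on the other side have force.

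- **The level is not fixed as CBO-level.** The scores come from individual questionnaires. Calling culture an organizational factor describes its subject, not how it is entered. A reader might infer that power for 2a is low outright; the documents do not support that, because with individual ratings the cap does not apply. This stands.
- **r = .30 and ICC = .03 are not shown to conflict.** A reader might infer a plain contradiction. But the outcome behind .03 is not named, and the protocol does not say whether it is unconditional or residual. If it is a residual ICC, r = .30 for a CBO-level predictor is possible: total ICC = .09 + .91 × .03 = .117; residual variance of a CBO mean = .0273 + .8827/8 = .1376; noncentrality √(12 × .09/.1376) = 2.80; power .71, the same as the stated dependence figure. On the same reading, the independence case does not rule out a CBO-level effect. This stands, and makes the low figures conditional.
- **The cap is narrower than it looks.** It limits the correlation with individual scores. Observed means of 8 staff can correlate up to √(.03/(.03 + .97/8)) = .445 with the predictor, and true CBO means up to 1. Nor is .34 a ceiling: other valid analyses reach .40 with 96 staff and .48 with 120. Equally, the pooled slope is mostly, not almost wholly, within-CBO.
- **Level of entry is often left to a statistical analysis plan.** True, but the protocol itself fixes the hypothesis, sample size, effect size, ICC and power. The printed power therefore already invites an organization-level reading, and standard-error adjustment alone does not separate the two effects.

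**Conclusion.** The point holds in conditional form. 2a asks about organizations, but its power statement is for individuals and the level of the predictors is unstated.

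- **Individual ratings:** the power calculation can apply, but the pooled slope draws roughly 51% to 87% of its information from within CBOs (assumed culture-score ICC of .50 to .05) and does not by itself support a statement about organizations.
- **CBO values, with .03 as the unconditional ICC of attitudes:** best-case power is about .31 to .40 with 96 staff and .36 to .48 with 120, against the stated .79/.71. It is about .2 if culture explains half the between-CBO variance.

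The second result moves strongly with the ICC (best case .15 to .84 over ICC .01 to .10 with 8 staff per CBO). It also treats one predictor at a time; culture and climate entered together, if correlated, would lower it. The change is worth making because it settles which question 2a answers, with data already being collected.

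**What to change.** 1. In the 2a HLM, enter each culture and climate score as two terms: the CBO mean and the staff member's deviation from it. Do the same for Leadership and Organizational Support in Aim 2.
2. Base any claim about organizations on the CBO-mean term, tested on about 10 df. Label the deviation term as perceived climate.
3. State that .79/.71 does not apply to the CBO-mean term. Give that term its own power, say what the .03 was measured on and whether it is unconditional, show a range of ICCs, and label the result exploratory.

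The cost is one extra term per predictor in a model already planned, and a restated power paragraph. No new data are needed. The downside is that the organizational claim becomes openly low-powered.

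### The regression power of .79 / .71 for Hypothesis 2a does not follow from its stated correlations of .30, which give about .63 / .55 with two predictors

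*Protocol*

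**What the plan says.** All of this is in Protocol section 8, Data Analysis and Interpretation, Aim 2.

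- Regression is assigned to Hypothesis 2a alone. Correlations serve 2c, 2e and 2f, and mediation tests serve 2b and 2d. Tests are two-tailed at .05.
- Sample sizes: "Under independence the sample size used was the total of 96", and "under dependence (ICC = .03) a functional sample size of 79.34 was used".
- Effect size for the regression: "the correlation between each predictor and the outcome and the correlation among the predictors was set to be *r* = .30". The text calls this a medium effect by bivariate conventions.
- Method: Monte Carlo in Mplus with 20,000 replications.
- Result: "The power for each regression coefficient was calculated to be .79 under independence and .71 under dependence".

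The power text does not say how many predictors were modelled. Hypothesis 2a names two, culture and climate.

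**The concern.** When predictors correlate with each other, each partial slope is smaller than the bivariate correlation, and collinearity widens its standard error. Power for a single coefficient should then fall well below the power for a simple correlation of the same size. The protocol gives .85 / .78 for a correlation of .30 and .79 / .71 for each regression coefficient. A loss of only 6 to 7 points looks too small.

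At stake is the accuracy of the planning statement for one Aim 2 hypothesis. A reader would take 2a to have nearly 80% power under independence to detect each coefficient at the stated medium effect.

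**Working it through.** **Inputs, all from the Aim 2 text except the predictor count:** alpha .05 two-tailed; N = 96 or 79.34; all correlations .30; k = 2 predictors (inferred from 2a).

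**Step 1. Check the shared inputs.**
- Functional N, using the cluster size of 8 given under Aim 1: 96 / (1 + 7 × .03) = 96 / 1.21 = 79.34, as stated.
- Correlation power by Fisher z: atanh(.30) = .3095. At N = 96, .3095 × √93 − 1.960 = 1.025, power .847. At 79.34, .3095 × √76.34 − 1.960 = .744, power .772. A noncentral t calculation gives .862 and .790. The stated .85 / .78 agree, so N, alpha and r are used consistently there.

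**Step 2. Regression power from the stated correlations.**
- Standardised slope: (.30 − .30 × .30) / (1 − .30²) = .21 / .91 = .2308.
- R² = 2 × .30 × .2308 = .1385; residual variance .8615.
- Noncentrality: slope × √(N × .91 / .8615). At N = 96: .2308 × √101.4 = 2.32. At 79.34: .2308 × √83.8 = 2.11.

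| Method | N = 96 | N = 79.34 (simulations: 79) |
|---|---|---|
| Noncentral t, N − 3 df | .633 | .550 |
| Normal approximation | .642 | .561 |
| Monte Carlo, 20,000 runs, ML Wald z | .636 | .565 |
| Monte Carlo, 20,000 runs, OLS t | .614 | .538 |
| Protocol | .79 | .71 |

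A second 20,000-run simulation gave .626 and .533. Monte Carlo error at 20,000 runs is about √(.79 × .21 / 20,000) = .003, so it cannot account for a gap of about 16 points (.79 − .633 = .157; .71 − .550 = .160).

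**Step 3. Try other readings (noncentral t or F).**

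| Reading | N = 96 | N = 79.34 |
|---|---|---|
| One predictor | .86 | .79 |
| Three predictors | .46 | .39 |
| Four predictors | .34 | .29 |
| Two predictors, one-sided alpha | .75 | .67 |
| Two predictors, omnibus F | .94 | .89 |
| Two uncorrelated predictors | .89 | .83 |
| Partial correlation .30 | .86 | .79 |
| Standardised slopes .30 | .89 | .82 |
| Raw slopes .30, predictor r .30, residual variance 1 | .793 | .711 |

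The .79 in the one-predictor row belongs to the functional N, not to 96.

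**Step 4. What the matching model implies.**
- Noncentrality: .30 × √(96 × .91) = 2.80 and .30 × √(79.34 × .91) = 2.55, giving .793 / .711. Monte Carlo with a Wald z test gives .793 / .719.
- Covariance of each predictor with the outcome: .30 + .30 × .30 = .39.
- Outcome variance: 1 + .09 + .09 + 2 × .30 × .09 = 1.234.
- Predictor-outcome correlation: .39 / √1.234 = .351, against the stated .30.

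**The case against.** **The predictor count is not stated.** True, so the replacement figures depend on it. The mismatch does not: no count from one to four reproduces the pair. Because the text refers to correlation among the predictors, at least two are needed, and two is the most favourable such count.

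**More staff may be enrolled than 96.** Section 9 plans about 120 and allows up to 135. With two predictors and independence, 120 gives .73 and 135 gives .78. But the power text fixes N at 96. With clusters of 10 and ICC .03, 120 staff give an effective 120 / 1.27 = 94.5 and power of about .63. Larger enrolment does not make the stated calculation right.

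**The consequence is limited.** This stands. 2a is one of six Aim 2 hypotheses, and the staff number is set as CBOs times staff per CBO, not from this power.

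**Stronger readings that a reader might infer, and that the documents do not support:**
- *That the mediation power is wrong as well.* The text requires 74 for power of .80 "when the effect sizes for both paths are medium" and gives .39 as that value. Both 79.34 and 96 exceed 74, and simulation at n = 74 with paths of .39 gives about .80. The statement is correct on its disclosed condition. That medium means .39 for paths and .30 for correlations is a difference of metric and convention, not an arithmetic error.
- *That Aim 2 as a whole is underpowered, or that 2a is a coin toss.* The correlation power for 2c, 2e and 2f reproduces, and .63 is not a coin toss.
- *That null culture or climate results will be over-read.* Nothing in the protocol says how a null coefficient would be interpreted.

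**Conclusion.** The stated power for the 2a regression coefficients is inconsistent with its stated inputs. For correlations of .30 throughout, two predictors and two-tailed alpha of .05, power is about .63 at N = 96 and .55 at the functional N of 79.34, against .79 and .71. The range across methods is about .61 to .64 and .53 to .57.

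The conclusion rests on reading r = .30 literally and on two predictors; a larger count widens the gap. A likely explanation is that .30 was entered as a raw slope with unit residual variance. That is inferred from the numerical match, since the protocol does not say so, and the mismatch holds whatever the cause. The error affects the planning statement for 2a only.

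**What to change.** In the Aim 2 power text, make one of two changes and state the number of predictors in either case:

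- keep correlations of .30 and restate the 2a power as about .63 under independence and .55 under dependence for two predictors; or
- keep .79 / .71 and restate the inputs as unstandardised slopes of .30, predictor correlation .30 and unit residual variance, noting that this implies predictor-outcome correlations of about .35.

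The authors' Mplus input should show which was meant. Leave the correlation and mediation statements as they are. The cost is a text edit, with no change to design, sample size or analysis; under the first option the stated power becomes less favourable.
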